**Protocol summary**

**Title: Development of an intervention integrating procedures combining hypnosis and virtual reality in the support of patients with myeloma and lymphoma**

**Objective**

Evaluate the effects of an RVH prototype in reducing anxiety and pain in transplant patients, and thus improving their long-term quality of life.

Gather user experience, satisfaction levels and recommendations for improvement of the RVH prototype from patients

Study drawing: Qualitative study of the RVH program user experience. And quantitative study to assess anxiety, pain, quality of life and fatigue.

Study population: haematology patients.

Sample size: 60 patients , 4 pre-test hematology patients

Study period: November 2024 - June 2025 .

Center responsible for the study: Centre de Recherche de l'Hôpital Maisonneuve-Rosemont (CR-HMR) - CEMTL, Montreal, Quebec, Canada.

Undesirable effects: none expected.

## **1. Issues**

### *Quality of life and cancer*

The measurement of quality of life is widely used in oncology. It provides a vision of the patient's overall health in relation to the cancer diagnosis and treatments, and their physical (e.g., pain) and emotional (e.g., anxiety) impacts, anxiety). Research with cancer patients has shown that quality of life is significantly altered by the disease and the treatments proposed to combat it. Altered quality of life in these patients is also reported to be a predictor of significant emotional distress.

### *Multiple myeloma, lymphoma and stem cell transplantation*

Multiple myeloma patients are among those most affected in terms of quality of life. This blood cancer, which affects plasma cells, subtypes of white blood cells found in bone marrow, is the second most common hematological malignancy, and is among the top ten cancer diagnoses requiring hospitalization. The cumulative time spent receiving treatment represents a significant burden for patients, and treatments have numerous adverse effects such as fatigue, nausea and weight loss. These patients are faced with stem cell transplantation after high-dose chemotherapy, a treatment that is recognized as one of the most stressful in cancer therapy, due to numerous adverse effects, including pain, and the uncertainty linked to the fear of graft failure. Studies have shown that the quality of life of these patients was greatly diminished during and immediately after autotransplantation, with a gradual improvement during the first year of follow-up. Most of them regain a better quality of life three to five years after transplantation, while others risk developing depressive and anxiety disorders in the medium to long term.

Studies report that 26% to 36% of patients with multiple myeloma report moderate to severe depressive symptoms in the first year after transplantation, and 18% of patients suffer from moderate to severe anxiety within the first 100 days after transplantation. These rates are far higher than the general population, in which the prevalence is around 5% for depressive disorders, and 3% to 6% for generalized anxiety disorders. In this context, patients with severely impaired quality of life and depression prior to stem cell transplantation are more likely to have impaired functional status after transplantation. These data indicate a major interest in improving patients' quality of life during transplantation. By offering psychosocial management involving complementary techniques aimed at improving patients' quality of life during the sensitive period of transplantation, we can aim to reduce levels of emotional distress and thus prevent psychopathological complications in transplant patients.

Lymphoma is generally classified into two main types: non-Hodgkin's lymphoma (NHL) and Hodgkin's lymphoma. Both types of lymphoma are common indications for stem cell autotransplantation. Together, lymphoma and myeloma account for over 95% of all indications for autologous transplantation. The cumulative time spent receiving treatments represents a significant burden for patients, and treatments have numerous adverse effects such as fatigue, nausea and weight loss (Lewandowska et al., 2020). As a result, blood cancer patients are among the worst affected in terms of quality of life.

### *Virtual reality hypnosis*

Psycho-oncology is a field of clinical intervention that has developed extensively over the last forty years. Among other things, it advocates the importance of offering complementary intervention programs to better support oncology patients. In contrast to the psychological interventions traditionally offered, complementary intervention programs can be more widely disseminated. They are more targeted, and aim, with certain benefits, at targets such as adaptation to cancer, treatment-related anxiety and patient pain.

Among existing programs, technology-based interventions such as virtual reality combined with hypnosis (VRH) have shown conclusive results in the few randomized controlled trials published to date. VRH has also shown promising effects on pain and reduction stress. A literature review on the usefulness of virtual reality (VR) during cancer-related medical procedures shows that it is adequate to distract from pain, even for very painful procedures, notably during chemotherapy. Nevertheless, the authors deplore the lack of studies on HVR in oncology, the absence of multiple measures (self-reported, physiological) and, more generally, the ability of these studies to report on factors predicting the effective use of this technology (adherence, feasibility, user experience). In addition, current HVR programs do not offer adaptability of the audio-visual environment in real time according to the patient's experience. New paradigms need to be created to integrate care in a more individualized way. In a person-centered approach to care, it is essential to place the patient and his or her needs at the heart of the environment's design, by proposing a tool adapted to the care context and capable of delivering beneficial effects at the lowest cost.

## **2. Objectives**

The main aim of this project is to reduce anxiety and pain, and thus improve the quality of life of patients with hematological cancer undergoing transplantation. The response we propose is in line with the recommendations issued by researchers in psycho-oncology and RVH, i.e., to develop an intervention program that can be widely disseminated and improve RVH protocols for better implementation.

For more than a year, clinicians, researchers, digital artists and patient partners have been working together to define an RVH program adapted to the problems of cancer, and usable by a large number of patients and caregivers. This program will have a number of advantages: it will enable individualized care through personalized hypnotic suggestions; it will enable the patient to be accompanied by the therapist through hypnosis verbatim pre-recorded; it will promote better absorption of the patient into the RVH experience; and it will optimize response to hypnotic suggestions for managing emotions and pain.

This study will evaluate the user experience, satisfaction and recommendations of this HVR program in patients with hematological cancer undergoing stem cell transplantation, which will provide new guidelines for improving HVR applications, as well as assessing the prototype's effects on reducing anxiety and pain, and thus improving their long-term quality of life.

Two complementary objectives were identified to evaluate the feasibility and effects of this program with a patient population highly affected by cancer, multiple myeloma, during a difficult treatment period, stem cell transplantation. In a first activity, we evaluated the user experience of this RVH program with patients in remission from cancer. This activity enabled us to define new guidelines for improving RVH applications. In the present project, we will evaluate the effects of RVH on quality of

life, patients' by modulating the negative emotions and pain experienced during stem cell transplantation anxiety and pain

### 3. Methodologies

#### *RVH intervention*

In collaboration with Super Splendide ([www.supersplendide.com](http://www.supersplendide.com)), a company specializing in the development of healthcare VR applications, our team, which includes two patient partners, has developed an intervention program (RVH) that combines VR and medical hypnosis (H) to facilitate the patient's absorption into a safe, benevolent imaginary world, in which they will be invited to live an experience that distracts them from their negative emotions and pain. The VR software was designed as part of another project developed in co-creation with palliative and long-term care settings (*Toujours dimanche*: <https://vimeo.com/643281872>). The development of *Toujours dimanche* involved over 200 volunteer hours of patient support, with the aim of adapting VR to the real needs of these patients. In the current project, the VRH program will offer a proactive approach to patient treatment. The virtual experience will be composed along the lines of a hypnosis session: 1- a soothing immersion will first be offered to anchor absorption, through calming audiovisual stimuli, 2- reaching a safe and relaxing space, representing a soothing natural environment (beach or park of the patient's choice), 3- two therapeutic stress management activities (putting all the stress you want to get rid of in a bag, and allow yourself to be carried by an imaginary horse, allowing you to escape to a safe place), 4- a physical discomfort modulation activity allowing you to reduce the sensation of discomfort in the part of your body afflicted by it, thanks to a visual representation of the pain that you extirpate from your own avatar and 5- return to an awake state of consciousness. The virtual environment increases the patient's sense of control, i.e. his ability to act and influence elements usually beyond his control, which in turn leads him to be more proactive in his therapy.

#### *Evaluation of the RVH program user experience*

**Participants:** A mixed study, combining quantitative and qualitative designs, was conducted with 40 partner patients in remission from cancer and 5 hospitalized hematology patients. For Activity 2, 60 participants will be recruited at the Maison-Neuve-Rosemont Hospital oncology, after verification of eligibility in the medical records and with the attending physician, who will have received prior authorization from the patient to be contacted by the research team. Inclusion criteria for participants are: 18 years of age or older, French-speaking, being treated for lymphoma or myeloma and requiring a hematology transplant. Exclusion criteria are: deafness, blindness, confusion or other disorders that may impair communication.

**Procedures Activity 1:** As shown in figure 1, two sequences will be conducted. In the first sequence, partner patients in remission from cancer will be invited to experiment with and give feedback on the program in order to improve the RVH device, based on their personal experience. In the second phase, a pre-test of RVH will be carried out with patients hospitalized for a hematology transplant. These two sequences will consist of three stages. Participants will be invited to 1- use the RVH intervention in the company of a psychologist; 2- complete a questionnaire evaluating the user's experience; 3- take part in individual semi-structured interviews, conducted by a duo made up of a patient partner and a researcher, in order to gather explanations complementary to the scores attributed in the questionnaires.

**Figure 1:** Activity 1 protocol: User experience study

[figure not shown]

Procedures activity 2: As shown in figure 2, participants will be randomly assigned in a controlled manner with a ratio of 1:1 to two conditions: RVH and a control condition (C) consisting of usual care and a waiting list. This allocation will be done by a random draw using the *Research Randomizer* program (<https://www.randomizer.org/>), which will be conducted by a person independent of the study. The first meeting will take place on arrival at the hospital, where the study presentation will take place, and the consent form will be signed. Participants will be asked to complete self-assessments at three time points: T0=pre-, session T1=accompanied, and T2=post-transplantation (1 months) and at T3=follow-up (3 months). According to studies carried out on multiple myeloma patients, T1 is conducted between D-14 and D-1 of the transplant stay.

[figure not shown]

Measurements Activity 1: We will use two questionnaires. The first assesses the participant's satisfaction through a questionnaire 19-item, which is evaluated on an Likert scale 11-level (0 = "strongly disagree" and 10 = "strongly agree" with the proposition). A questionnaire (UEQ, 24 items, 7-level Likert) will also be used to assess the six components of user experience: usability, usefulness, hedonic qualities (e.g., originality), attractiveness, sense of presence, resulting emotions. The interview grid will be based on the same items as these questionnaires, enabling participants to develop their responses.

Measurements Activity 2: At T0, we will collect sociodemographic and data clinical from patients, including age, gender, sex, occupation, marital status, socioeconomic status and clinical diagnosis. We will also assess participants' expectations in the form of the question do you have any expectations regarding the use and efficacy of RVH? . At T0, T2 and T3, we will collect data on quality of life, anxiety, pain, fatigue and depression. The FACT-BMT is a validated scale for patients undergoing bone marrow transplantation. It contains 50 items divided into 5 subscales: Physical Well-Being, Social/Family Well-Being, Emotional Well-Being, Functional Well-Being and Bone Marrow Transplant Subscale on a 5-point Likert scale ranging from 0 = not at all to 4 = very much. The *Hospital Anxiety Depression Scale* (HADS) is a scale validated in French for cancer, which assesses participants' anxiety-depression. It is made up of 14 items: 7 items determine the degree of anxiety and the other 7, the degree of depression. The score of each subscale is calculated by summing the score of each item, which varies between 0 and 3, with each subscale reaching a maximum score of 21. Fatigue will be assessed using the 10-item version of the Multidimensional Fatigue Inventory (MFI-10) adapted to cancer. It is scored on a 5-point Likert scale ranging from 1: "strongly disagree" to 5: "strongly agree". Pain is assessed using the Brief Pain Inventory (BPI). This scale consists of 8 items on a 10-point Likert scale assessing pain severity, impact of pain on daily functions, location of pain, pain medication and extent of pain relief over the past 24 hours or week. At transplantation, we will use the diary with 11-level Scales before and after each RVH procedure to assess the direct effect of the procedure on pain, anxiety, enjoyment, i.e., the ability to enjoy oneself during the intervention, absorption, i.e., the tendency to become totally involved in a perceptual and imaginative experience, dissociation, i.e., a mental separation of components of the experience and fatigue. After each intervention, the Simulator Sickness Questionnaire, a scale validated in French, assesses symptoms of cybermalaise linked to immersion in VR. It contains 16 items divided into two subscales: nausea and oculomotor, which the participant must qualify as "not at all" (score 0), "a little" (score 1), "moderately" (score 2) or "severely" (score 3). . At T3, we will collect patients' level of satisfaction through a 19-item questionnaire that is evaluated on an 11-point Likert scale (0 = "strongly disagree" and 10 = "strongly agree" with the proposal). This questionnaire has been used in other studies to assess participant satisfaction with an intervention program^37. We will collect patients' levels of expectation and satisfaction using a five-level rating scale (1 = "not at all satisfied", 5 = "very satisfied") and explanatory interviews. Satisfaction interviews will also be conducted with caregivers in the hematology departments involved. The outcome secondary will be the change from T0 to T2 and T3 in the scores FACT-BMT, MFI and HADS-D, while the main outcomes primary will be changes from T0 in the degree of anxiety, of pain, . Changes in measures of pain, anxiety, amusement, absorption, and dissociation (logbooks completed during the two-week transplant stay) will also be considered secondary outcomes. We expect to At T3, we will assess acceptability and user experience with the User Questionnaire Experience (UEQ). This validated questionnaire is composed of 24 items that are evaluated on a 7-level Likert scale. It will be used to assess the six components of user experience: usability, usefulness, hedonic qualities (e.g., originality), attractiveness, sense of presence, resulting emotions. Sample size justification: At HMR, around 100 patients a year are treated for multiple myeloma and undergo cell transplantation stem. The sample size was also determined using a power calculation to ensure a sufficient probability of detecting a statistically significant effect, if any. We used an alpha significance level of 0.05 and a power (1 - B) of 0.95. The expected effect was estimated from \_\_\_\_\_, with an effect size of \_\_\_\_\_. Based on these

parameters, the power calculation suggests that a sample size of 60 participants is required to detect this effect with adequate power. The software \_\_\_\_ was used to perform this calculation. The sample size also takes into account a potential loss rate of \_\_\_\_%, to compensate for drop-outs and missing participants. .

Analyses Activity 1: The scores obtained on the questionnaire items will be compared with the theoretical mean of 6, i.e. the neutral level of acceptability on a scale from 0 to 10. An average above this threshold will be interpreted as a good experience of RVH. Analysis of the interview verbatim will enable us to make an open-ended assessment of the RVH experience. Significant narratives in each theme will be used to illustrate participants' opinions and experiences. Qualitative analysis of the narratives will enable us to identify positive and negative aspects, as well as avenues for improving the program. NVIVO software will be used for these analyses. This study will enable relevant modifications to be made to the program prior to the clinical effects study.

Analysis activity 2 :

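### Enjoyment is defined as felt during the session, so its pre-session diary rating and before-after change cannot be interpreted; absorption and dissociation need state wording

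*Protocol*

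**What the plan says.** The relevant text is in the protocol, section 3, under *Evaluation of the RVH program user experience*, in the paragraph Measurements Activity 2.

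- **Timing and purpose.** "we will use the diary with 11-level Scales before and after each RVH procedure to assess the direct effect of the procedure on pain, anxiety", followed by enjoyment, absorption, dissociation and fatigue.
- **Definitions.** "enjoyment, i.e., the ability to enjoy oneself during the intervention, absorption, i.e., the tendency to become totally involved in a perceptual and imaginative experience"; and "dissociation, i.e., a mental separation of components of the experience and fatigue". In the last of these, fatigue is the sixth diary item and not part of the definition.
- **Outcome status.** "Changes in measures of pain, anxiety, amusement, absorption, and dissociation (logbooks completed during the two-week transplant stay) will also be considered secondary outcomes". Amusement appears to be the item called enjoyment in the diary list, since nothing else there matches it.

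The *Quantitative* subsection of the Activity 2 analyses plans correlations on the variables from the transplant phase, as the measure of RVH's immediate effects. It also lists absorption, dissociation and enjoyment among the variables controlled for in the MANCOVA, without saying which rating is meant. Under Procedures activity 2, control patients receive usual care and are wait-listed. No diary is described for them.

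**The concern.** A before-after difference is useful only if the same quantity exists and can be rated at both times. Pain, anxiety and fatigue meet that condition. Enjoyment does not, because its definition ties it to an intervention that has not yet begun when the first rating is made. A patient asked beforehand might enter 0, state an expectation, recall a previous session or leave the item blank, and the protocol does not say which is wanted.

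The resulting difference could then be reported as an immediate effect of RVH when part or all of it reflects how the item was read. No control-arm diary is described that would expose this. Analysis cannot repair it later, because a rating collected without a stated referent cannot be given one afterwards. Item definition, rating time and outcome metric are set in this protocol, so the matter is not one that can be left to a statistical analysis plan.

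**Working it through.** The plan gives no figure on this point, so there is nothing to reproduce. The check sets each definition against the use made of it.

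**Step 1. Can the item be rated before the session, and is change within a session a sensible target?**

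| Diary item | Definition in the protocol | Ratable beforehand? | Fits a within-session change? | Named change outcome? |
|---|---|---|---|---|
| Pain | none needed | yes | yes | yes |
| Anxiety | none needed | yes | yes | yes |
| Fatigue | none needed | yes | yes | no |
| Enjoyment (amusement) | tied to the intervention | no, as defined | no | yes |
| Absorption | a tendency, not limited to RVH | yes | doubtful: a disposition is a poor target for change in one session | yes |
| Dissociation | concerns an experience not identified | yes if current experience is meant; no if the RVH experience is meant | only if worded as a current state | yes |

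Of the five named change outcomes, two are sound (pain, anxiety), one is uninterpretable as defined (enjoyment), and two depend on wording the protocol does not give (absorption, dissociation).

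**Step 2. What the missing referent does to the enjoyment score.** Change = post-session rating − pre-session rating. Assume that the 11 levels run from 0 to 10 and take a post-session rating of 6. These values are illustrative and do not come from the protocol.

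- Patient enters 0 because nothing has happened yet: 6 − 0 = +6.
- Patient states an expectation of 6: 6 − 6 = 0.
- Patient states an expectation of 8: 6 − 8 = −2.
- Limits of the scale: 6 − 0 = +6 and 6 − 10 = −4.

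The same session experience gives changes from +6 to −4. In the special case where the earlier answer is 0, change equals the post-session score and cannot be negative.

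**Step 3. Use as control variables.** The only ratings of these three items that the protocol describes are tied to RVH sessions, and the list of T0 measures does not include them. A model comparing the two arms therefore has no described value of them for control patients. Enjoyment as defined cannot have one in a patient who has had no session.

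**The case against.** Several counter-arguments deserve weight.

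**Item wording is not shown.** The protocol gives short glosses, not the diary items or their instructions, and a pre-session item worded as a current state would be compatible with the text for absorption and dissociation. This stands, and it is why the fault for those two is one of fit and not of impossibility. It does not rescue enjoyment, whose definition itself refers to the intervention.

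**A reader might infer more.** One might conclude that all three items lack a valid pre-session value, that these secondary outcomes are artefacts, and that a large improvement is guaranteed. The documents do not support this. A tendency can be rated at any time, dissociation can be rated beforehand if current experience is meant, and nothing shows how patients would answer. Nor can absorption be both a stable disposition that one session leaves unchanged and an unanswerable item scored 0 beforehand.

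**The change may be across sessions.** The outcome sentence does not say that change runs from before to after a session. It could mean the course over the two-week stay, which needs no pre-session value, and the only analysis stated is correlation. This is a fair reading of that sentence, but the diary sentence still prescribes a pre-session enjoyment rating for the purpose of showing a direct effect.

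**Post-session-only ratings lose information.** For dissociation, a pre-session rating could separate what was already present from what the session produced. This stands, so dropping pre-session absorption and dissociation is one option and not a requirement.

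**Conclusion.** The point holds fully for enjoyment. As defined it has no pre-session value, and a before-after change in it cannot be interpreted as an effect of RVH. It holds in a weaker form for absorption and dissociation, whose definitions do not suit a within-session change measure unless the items are worded as current states.

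The size is one of five named change outcomes uninterpretable as defined and two more under-specified. The numerical example shows only that the enjoyment score depends on how the first item is read. It does not estimate the size or likelihood of a bias. The conclusion assumes that amusement and enjoyment are the same item and that the diary items follow the printed definitions.

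Diary pain, anxiety and fatigue are unaffected, as are the primary outcomes (changes from T0 in anxiety and pain). The efficacy model is touched only through its control variables. This is a modest fault in secondary outcomes, but it has to be corrected in the diary before data are collected.

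**What to change.** In Measurements Activity 2:

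- **Enjoyment:** rate it once, after each session, and report it as a post-session level. Remove amusement from the change outcomes, and use one name for the item throughout. If the course over the stay is of interest, describe it from the post-session ratings.
- **Absorption and dissociation:** choose one of two routes. Either word both items as current states, with the same 'right now' referent at both times, and keep the change scores; or rate them after the session only and remove them from the change outcomes.
- **Pain, anxiety and fatigue:** leave as they are.

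In the *Quantitative* subsection, state which rating of absorption, dissociation and enjoyment enters the MANCOVA. Session-tied ratings are not described for control patients, so either specify a measure taken in both arms before any session or take the item off the list. Only removal is open to enjoyment as now defined.

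The cost is a diary edit and a few sentences of protocol text, with at least one fewer rating per session for patients in a transplant stay. The downside is that there is no change score for enjoyment, nor for absorption and dissociation if the second route is chosen. On the second route the plan also gives up a pre-session reference for dissociation, which is a reason to consider the first.

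### The Simulator Sickness Questionnaire is given only after RVH sessions, with no pre-session or control-arm value, so cybersickness cannot be separated from treatment symptoms

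*Protocol*

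**What the plan says.** All of this is in the protocol; no statistical analysis plan is at hand.

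- **Timing of the SSQ** (section 3, Measurements Activity 2): "After each intervention, the Simulator Sickness Questionnaire, a scale validated in French, assesses symptoms of cybermalaise linked to immersion in VR". No SSQ before a session is stated.
- **Content of the SSQ** (same paragraph): "It contains 16 items divided into two subscales: nausea and oculomotor". Each item is scored 0 to 3.
- **Timing of the diary** (same paragraph, just before the SSQ): "diary with 11-level Scales before and after each RVH procedure to assess the direct effect of the procedure". It covers fatigue, dissociation, absorption, enjoyment, anxiety and pain. It has no nausea or visual-symptom item.
- **Comparator** (section 3, Procedures activity 2): patients are "randomly assigned in a controlled manner with a ratio of 1:1 to two conditions", the second being "a control condition (C) consisting of usual care and a waiting list".
- **Background symptoms** (section 1, on myeloma, lymphoma and transplantation): "treatments have numerous adverse effects such as fatigue, nausea and weight loss". Section 4 adds that treatment side effects may make VR hard to use in this population.
- **Protocol summary**: "Undesirable effects: none expected".

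The SSQ is not among the named primary or secondary outcomes, nor among the dependent variables of the planned MANCOVA.

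**The concern.** The SSQ is there to pick up symptoms produced by immersion. To do that it needs a reference value: the same patient before the session, or a comparable patient who had no session. The protocol provides neither. The symptoms it scores include nausea, which the protocol itself lists as an effect of treatment, and the sessions fall in or around the transplant stay.

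The error could run either way. Treatment nausea could be read as cybersickness, making RVH look poorly tolerated. Real cybersickness could be dismissed as treatment nausea. The protocol presents this study as a step towards wider multicentre studies, so an uninterpretable cybersickness result would be carried forward.

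This is a question of what is collected, not of how it is analysed. A statistical analysis plan could choose how to summarise the SSQ but could not create a pre-session value that nobody recorded.

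**Working it through.** The protocol gives no figure for cybersickness or nausea, so there is nothing of its own to reproduce. The argument rests on the measurement schedule; the numbers below only illustrate it, with assumed rates.

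**1. What each schedule identifies.** For one patient and one session, let B be the background symptom score before the session, C the change in background symptoms during it, and V the effect of immersion.

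- Post-session SSQ only (as planned): B + C + V.
- Post minus pre, same instrument: (B + C + V) − B = C + V.
- Post minus pre, less the same difference over a matched period without a session: V, on average.

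The plan stops at the first line, where B is unknown. The diary, for its own items, reaches the second.

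**2. Illustration in rates.** Let b be the share of patients with background nausea, and q the share of the rest in whom RVH induces it. Assume that RVH does not relieve nausea and that background nausea does not change during the session. The post-session share is then

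p = b + (1 − b)q.

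Suppose p = 0.40 is observed.

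- b = 0.40, q = 0: 0.40 + 0.60 × 0 = 0.40.
- b = 0.20, q = 0.25: 0.20 + 0.80 × 0.25 = 0.40.
- b = 0, q = 0.40: 0 + 1 × 0.40 = 0.40.

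Solving for q gives q = (p − b)/(1 − b), so with b unknown any q from 0 to 0.40 fits the data. More patients would not narrow this range, because the problem is identification and not precision.

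**3. Would giving the SSQ to controls be enough?** With 60 patients allocated 1:1 there are 60/2 = 30 per arm. Take two-sided alpha 0.05, 80% power and no loss. The smallest detectable share p₁ against background b solves

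p₁ − b = 1.96·√(2p̄(1 − p̄)/30) + 0.84·√([b(1 − b) + p₁(1 − p₁)]/30), with p̄ = (b + p₁)/2.

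| Assumed background b | Smallest detectable p₁ |
|---|---|
| 20% | 54% |
| 40% | 75% |
| 60% | 91% |

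A control-arm SSQ would supply a comparator, but at this size a single between-arm comparison would show only excesses of about 31 to 35 percentage points. That favours pairing within patients as the practical change.

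**The case against.** The strongest reply is that the SSQ is ancillary and that harm is watched elsewhere. Much of this stands. A reader might infer that the trial cannot tell whether RVH causes harm at all; the protocol does not support that. Quality of life, fatigue, pain, depression and anxiety are collected at T0, T2 and T3 and compared between randomised arms, and the diary gives paired values around each session. Interviews, the satisfaction questionnaire and the user-experience questionnaire could also register poor tolerance. None of these measures nausea or visual symptoms around a session, however, and T2 and T3 come one and three months after transplantation.

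Other limits also stand:

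- A reader might infer that patients are already nauseated when a session starts. Nausea is named as a treatment effect, with no rate and no timing relative to sessions. It is likely but not documented.
- A reader might infer that half of the SSQ is nausea. The protocol names two subscales but gives no split of the 16 items.
- The protocol sets no tolerability criterion for going on to later studies.
- Expecting no undesirable effect while still monitoring for one is not a strict contradiction. The summary line is a tension in wording and does not cause the attribution gap.
- The Activity 2 figure is not reproduced in the text available, so a fuller schedule there cannot be ruled out.

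None of this supplies a reference value for the SSQ.

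**Conclusion.** The point holds for cybersickness symptoms only. As written, the SSQ is completed after sessions in the RVH arm, with no pre-session or control value, so its nausea and oculomotor scores cannot be attributed to immersion as distinct from treatment. Other harms can still be seen through the T0/T2/T3 scales and the diary, and no primary or secondary outcome is affected.

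The size is unknown, because the protocol gives no background rate. In the illustration, a 40% post-session nausea rate is compatible with RVH inducing nausea in anywhere from none to 40% of otherwise unaffected patients. The conclusion itself does not depend on those rates. It rests on the schedule as stated in the text and on treatment nausea being present in some patients at the time of sessions.

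This is a cheap improvement, not a flaw that undermines the trial.

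**What to change.** - Give the same SSQ immediately before as well as after each RVH session, alongside the before/after diary, and report cybersickness as the within-session post-minus-pre change.
- Use the same items at both times and at every session, so that the change has one definition throughout and covers both subscales.
- State that pairing reduces confounding but does not fully remove it: background symptoms can change during a session, and there is no control session to show by how much.
- Reconcile the summary's statement on undesirable effects with the monitoring of cybersickness in Measurements Activity 2.

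The cost is 16 short extra items per session (32 in place of 16) for ill patients, plus a line of protocol wording. If that burden is too great, pair a fixed subset of SSQ items, the same before and after every session.
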